### Study aims

The purpose of this phase II RCT is to test the efficacy and additive/synergistic effects of an exergames intervention (simultaneous moderate intensity cycling and cognitive training), in comparison to cycling only and attention control (stretching) on cognition and aerobic fitness in older adults with SCD. The specific aims and hypotheses of the study are described as follows:
Aim 1: Determine the efficacy of the exergame in older adults with SCD.Hypothesis: Exergame will improve global cognition more than cycling only and attention control.Aim 2: Assess the distraction effect of an exergame on aerobic fitness.Hypothesis 2a: Exergame participants will achieve similar gains in aerobic fitness to cycling participants.Hypothesis 2b. Exergame participants will achieve similar exercise intensity targets to cycling participants.

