## Methods

### Design

The RCT will use a single-blind, 3-parallel group design, guided by CONSORT [31] and SPIRIT [32] guidelines (*n* = 96). We will use a 2:1:1 allocation ratio to randomize 48 subjects to exergame, 24 to cycling only, and 24 to attention control within age strata (< 75 and ≥ 75 years) and using permuted blocks of 4 and 8 participants. Based on our previous studies, we anticipate screening approximately 288 individuals to enroll 96 participants. Cognition and aerobic fitness will be assessed at baseline and 3 months. This study was approved by the university Institutional Review Board and registered at ClinicalTrials.gov on 17 March 2020 (study identifier NCT04311736).

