#### Sample size and power

Enrollment of 96 subjects with 12% attrition at 3 months will give us 80% power to detect a .85 effect size between exergame and attention control.

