Aim 1: Determine the efficacy of the exergame in older adults with SCD. To test our hypothesis that exergame will improve global cognition more than cycling only and attention control, the ANOVA will be performed. If statistically significant results are identified, then we will perform post hoc analysis to determine how the changes in cognition differ between groups. If homogeneity of variances are supported across the three groups, we will conduct Tukey’s honestly significant different post hoc test. If homogeneity of variances are violated, then we will perform the Games Howell post hoc test. If significant covariates are identified, then analysis of covariance (ANCOVA) will be used instead. Linear simple and multiple regressions will be performed to assess association between the effects of exergames on global cognition and aerobic fitness. A *p* value < 0.05 will be used to determine statistical significance. Effect size (EF) calculated as EF = (mean exergames group − mean stretching group)/SD (stretching group) will be used to assess the clinical significance of the effects of exergames on cognitive and aerobic fitness outcomes listed above.Aim 2: Assess the distraction effect of exergame on aerobic fitness. Our hypothesis that exergame participants will achieve similar gains in aerobic fitness to cycling participants will be analyzed similarly to aim 1 hypothesis using ANOVA and post hoc test. In addition, heart rate monitor data will be utilized to compute intensity dose, to compare objective effort given during exergame and cycling only sessions. We hypothesize that the average %HRR achieved by exergame participants will not be significantly different compared to cycling only participants. A standard formula will be used to quantify the intensity dose and is as follows. Percent HRR (%HRR) averaged in each session will be calculated from the following variables (EHR = exercise session average heart rate, PHR = peak heart rate from SWT, and RHR = resting heart rate from SWT) and formula: %HRR = [(EHR − RHR)]/(PHR − RHR)]. The %HRR will be averaged across all sessions to give a quantifiable index of intensity to be used as a surrogate measure of distraction. Differences between exergames and cycling only groups on average %HRR will be assessed by independent *T* test.

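### Aim 2 sets similarity hypotheses but assesses them with difference tests at p < 0.05 and no margin, so a non-significant result would be read as similarity

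*Protocol article*

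**What the plan says.** Under Study aims, the Protocol article states two hypotheses for Aim 2. Hypothesis 2a is "Exergame participants will achieve similar gains in aerobic fitness to cycling participants". Hypothesis 2b is "Exergame participants will achieve similar exercise intensity targets to cycling participants".

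Under Statistical analyses, 2a "will be analyzed similarly to aim 1 hypothesis using ANOVA and post hoc test". That means an omnibus F test across the three arms and, if it is significant, Tukey's test (or Games-Howell if variances are unequal). For 2b, average %HRR is named as a surrogate for distraction. The hypothesis is restated as "We hypothesize that the average %HRR achieved by exergame participants will not be significantly different compared to cycling only participants", and the test is a two-sample t test: "Differences between exergames and cycling only groups on average %HRR will be assessed by independent". The threshold given in that section is that a *p* "value < 0.05 will be used to determine statistical significance".

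The article states no equivalence or non-inferiority margin, and no rule based on a confidence interval. The only power statement, under Sample size and power, concerns exergame against attention control. It does not concern exergame against cycling, which is the contrast Aim 2 needs.

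**The concern.** A difference test is built to reject equality. Failing to reject shows only that the data did not exclude equality. It does not show that the arms are close. When the hypothesis itself is non-significance, a smaller sample, noisier measurement or more dropout makes it easier to confirm, which is the wrong direction.

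This is not detail left to a separate analysis plan. The article names the tests, the threshold and, for 2b, the wording of success. An analysis plan that added a margin would be changing that text.

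The assessment of distraction is one of the trial's two aims, and the Discussion says the results are to inform phase III trials. An exergame that costs some aerobic fitness could be carried forward as equal to cycling because this trial could not see the cost. For 2a there is a second ambiguity: two arms that both gain nothing are also not significantly different, although the hypothesis speaks of similar gains.

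**Working it through.** **Inputs.** Design: "randomize 48 subjects to exergame, 24 to cycling only, and 24 to attention control". Sample size and power: "Enrollment of 96 subjects with 12% attrition at 3 months". Evaluable numbers are 48 × 0.88 = 42.2 and 24 × 0.88 = 21.1, so 42 exergame, 21 cycling and 21 control. Alpha is 0.05, taken as two-sided because sidedness is not stated. Effects are in SD units of the analysed variable, since the article gives no SD for shuttle walk test (SWT) distance or %HRR. The 0.5 SD benchmark is an assumption, so a range is shown.

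**The plan's own figure.** The article states 80% power at an effect size of 0.85 for exergame against control. At 42 vs 21 the noncentral-t power is 87.9% at two-sided 0.05, 80.9% at two-sided 0.025, and 78.4% with Tukey's critical value for three groups. The 80% is therefore reproducible if some multiplicity adjustment was used. Nothing below depends on which one.

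**Precision of exergame minus cycling.** SE = √(1/42 + 1/21) = 0.267 SD. The 95% CI half-width is t(0.975, 61 df) × SE = 2.00 × 0.267 = 0.53 SD. An observed deficit of half an SD would therefore still be non-significant in the t test.

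**2b, t test on mean %HRR.** Probability of p > 0.05, from the noncentral t with noncentrality d / SE:

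| True loss (SD) | 42 vs 21 | 48 vs 24 |
|---|---|---|
| 0.3 | 80% | 78% |
| 0.4 | 69% | 65% |
| 0.5 | 55% | 49% |
| 0.6 | 40% | 34% |
| 0.85 | 12% | 8% |

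The second column matters because %HRR is averaged over sessions and does not need a 3-month visit.

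**2a, F test then Tukey on SWT fitness.** Simulated at 42/21/21 with equal variances and no baseline adjustment (200,000 runs). Probability that exergame and cycling are not declared different:

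| True gain: exergame, cycling, stretching (SD) | Not different |
|---|---|
| 0, 0.5, 0 | 70% |
| 0, 0.6, 0 | 56% |
| 0.3, 0.6, 0 | 89% |
| 0, 0.85, 0 | 22% |
| 0, 0, 0 | 98% |

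Tukey alone gives 69% in the first row, so the omnibus gate adds only about one point. Most of the loss comes from the sample size and Tukey's critical value.

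**What a margin would require.** For a non-inferiority test (one-sided 0.025, true difference 0, 42 vs 21, no baseline adjustment), normal-approximation power is Φ(margin / 0.267 − 1.96):

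| Margin (SD) | Power |
|---|---|
| 0.3 | 20% |
| 0.4 | 32% |
| 0.5 | 46% |
| 0.6 | 61% |
| 0.75 | 80% (79% by exact t) |
| 0.85 | 89% |

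For 80% power at a 0.5 SD margin, 96 + 48 evaluable participants would be needed.

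**The case against.** A reader might infer that the rule yields similarity with high probability whether or not it is true, or that it usually misses a half-SD loss on both outcomes. The figures do not support either. At a loss of 0.85 SD, the only effect size in the article, the t test misses 12% and F-then-Tukey 22%. For %HRR at 0.5 SD the chance is 55%, or 49% if everyone randomised contributes session data, so it is close to a coin flip. Only the SWT result at 0.5 SD is clearly more often missed than found.

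Other points stand in part:

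- **Relevance of 0.5 SD.** Both arms cycle to the same supervised, heart-rate-guided prescription, progressed partly in steps of 5% of HRR. If the SD of mean %HRR were 5 to 10 points (an assumption), 0.5 SD would be 2.5 to 5 points, no more than one step. Missing that may not matter. But the article does not say what difference would matter, and without that a null result cannot be interpreted.
- **No gains in any arm.** The article commits to an exergame-versus-stretching effect size that covers aerobic fitness, so an absent exergame gain would be visible. It is not tied to 2a, and no corresponding effect size is given for cycling.
- **What the article declares.** It nowhere says that a finding of no distraction will be announced, and for 2a it does not spell out that a non-significant post hoc test means similarity. That reading is an inference from the hypothesis and the test chosen for it. For 2b the wording is explicit.
- **Phase and status.** This is a phase II trial meant to supply effect sizes, and the article is inconsistent on whether fitness is primary (Abstract) or secondary (Primary and secondary outcomes). That lowers the urgency, and it also favours reporting by estimation.

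**Conclusion.** The concern holds at moderate strength. Two similarity hypotheses are paired with difference tests, no margin is set, and one of the two is worded as non-significance. For small to moderate losses this gives little protection: at 0.5 SD, about 70% non-significant for SWT fitness and about 50–55% for %HRR. For large losses it gives reasonable protection. A 2a result of no difference also cannot separate equal gains from no gains.

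The figures rest on 12% attrition in each arm (with none as the alternative for %HRR), two-sided 0.05, equal variances, no baseline adjustment and a benchmark not taken from the article. Baseline adjustment would improve the SWT figures. The flaw in the inference does not depend on any of these. It should be fixed, but it does not undermine the trial's design or Aim 1.

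**What to change.** For 2a and 2b, report the exergame-minus-cycling difference with a 95% CI: SWT change adjusted for baseline, and mean %HRR. State that similarity will not be concluded from p > 0.05, and reword the 2b hypothesis accordingly.

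Claim similarity or non-inferiority only if the CI excludes a margin that is justified and fixed before unblinding, in metres and in %HRR points. Say whether the claim is two-sided (equivalence) or one-sided (non-inferiority), since the word similar could mean either. The planned size gives about 80% power for non-inferiority only with a margin near 0.75 SD without baseline adjustment. If no such margin can be justified, restate Aim 2 as estimation and drop the similarity conclusion. That may well be the realistic course at this size.

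Alongside 2a, show the SWT difference from stretching for both the exergame and the cycling arm, so that equal gains can be told from no gains. This is for interpretation and need not be an added success criterion.

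The cost is a change of analysis wording and, if a claim is wanted, the work of justifying a margin. No new participants or data are needed, and the article says the trial was still open for enrolment at submission. The downside is that the similarity claim becomes harder to reach.

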### Ethics

This study was approved by the university Institutional Review Board (IRB), and any amendments or subsequent changes or to the protocol will be submitted to the IRB for approval. Written consent takes place during the in-person interview. Participant’s capacity to consent will be assessed by staff through use of the UCSD Brief Assessment of Capacity to Consent form (UBACC) [54] modified for exergame. A participant must score a “2” on items 1, 2, 4, 6, 7, and 9 on the assessment for inclusion in the study. If a participant scores less than 2 on any of these items, the staff will re-explain the study, and then ask the participant to return on another day to retake the UBACC. If the participant scores < 2 on any of these items again, then the subject is not eligible to participate in the study. Consenting will be an ongoing process during the study as verbal consent will be obtained at the beginning of each activity session. Participation in exercise is known to cause musculoskeletal pain or discomfort during exercise or 24–48 h following exercise (due to commonly seen delayed onset muscle soreness). Study-related, anticipated adverse events such as these will not be reported to IRB; however, all study-related unanticipated adverse events (such as cardiopulmonary events) will be reported to the IRB and funding agency within 5 business days of the event.

### Dissemination

Findings from the RCT will be disseminated through presentations and publications. Participants and their family members will receive a copy of the published main findings. All manuscripts will be authored by the study team and authorship will follow the established publication guidelines such as those of the International Committee of Medical Journal Editors. Access to the final trial data set will follow the guidelines of the National Institute on Aging.

## Discussion

Developing interventions, with strong potential to prevent or delay the onset of AD in persons with SCD is critical. Aerobic exercise and cognitive training represent two promising interventions; however, their synergistic effects on preventing AD have not been evaluated. Our study will develop a novel, apple-TV, and iPad-based cognitive training that is immersive, naturalistic, and similar in tasks to real life, and therefore increases the ecologic validity of the treatment [29]. It is cognitively challenging but also increases exercise enjoyment.

All attempts have been undertaken to ensure the highest quality of study design and delivery of the Exergames Study. First, RCTs are considered the gold standard design for determining the causal effect of an intervention on an outcome. Alternatively, intervention trials commonly employ usual care or waitlist control groups or cross-over design. Usual-care or waitlist controls preclude assessing the Hawthorne or placebo effect of exergames, while cross-over designs are ideal for interventions without carry-over effects, which is also not the case for exergames. In addition, we have built in four strategies to prevent unblinding, another potential problem occurring in RCTs. The four unblinding prevention strategies include (1) assessors will not interact with other staff who are not blinded (i.e., exercise interventionists) and will participate in separate meetings, (2) investigators will be blinded to group assignments, (3) participants will be blinded to the study aims and reminded as needed not to discuss their experiences with the outcome assessor, and (4) randomization will be completed using permuted blocks. Additionally, age is a known, strong factor affecting cognition. While our aims are not focused on age, we will stratify enrollment by age to equalize age distribution across groups [55, 56].

In summary, the Exergames Study will be the first RCT to examine the additive/synergistic effects of a novel simultaneous moderate intensity, supervised aerobic exercise + cognitive training intervention on cognition and aerobic fitness. This study looks to advance AD prevention research by providing precise immediate and long-term effect-size estimates of an aerobic exercise intervention delivered with simultaneous cognitive training to inform future fully powered, large scale phase III RCTs.

## Trial status

ClinicalTrials.gov identifier NCT04011267, version 1.0, 17 March 2020. Registered on 17 March 2020 (reterospectively registered) and at the time of manuscript submission has not been updated. The status of the trial at the time of manuscript submission is open for enrollment. Participant enrollment began on 27 December 2019 and we expect enrollment accrual to complete in 2022.

## Data Availability

Not applicable

## Abbreviations

ACSM: American College of Sports Medicine
AD: Alzheimer’s disease
ANCOVA: Analysis of covariance
BAI: Beck’s Anxiety Inventory
CONSORT: Consolidated Standards of Reporting Trials
EF: Effect size
Gas-10: Geriatric Anxiety Scale – 10-item version
HIPPA: Health Insurance Portability and Accountability Act
HR: Heart rate
HRR: Heart rate reserve
ID: Identification
iPAD: Interactive personal application device
IRB: Institutional review board
MCI: Mild cognitive impairment
NIHTB-CB: NIH Toolbox Cognitive Battery
PSMT: Picture Sequence Memory Test
RAVLT: Auditory Verbal Learning Test (Rey)
RCT: Randomized controlled trial
REDcap: Research Electronic Data Capture
RPE: Rating of perceived exertion
SAS: Statistical Analysis System
SCD: Subjective cognitive decline
SPIRIT: Standard Protocol Items: Recommendations for Interventional Trials
SPSS: Statistical Product and Service Solutions
SWT: Shuttle walk test
UBACC: USCD Brief Assessment of Capacity to Consent
VRCT: Virtual reality cognitive training
YMCA: Young Men’s Christian Association
